## 2 Methods and analysis

### 2.1 Study design and timing

This observational study, uses a cross-sectional design due to its screening nature. The data for the present research will be derived from a selective LC-MS/MS IEM screening of 1,500 clinical-risk children aged 1 day to 18 years and 750 healthy controls of the same age to set reference values for 15 AAs, 35 ACs, and SuAc. The main points of the research are presented in Figure 1 (Flowchart of the study.)

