### 2.3 Methods and procedures

#### 2.3.1 Mass spectrometry analysis. specimen collection and storage

Neonatal whole blood samples are taken from high-risk and healthy infants no earlier than 3 h after feeding by heel prick with a heel stick. Five drops of whole blood (∼75 µL each) are put onto Guthrie cards, Ahlstrom 226 filter paper, PerkinElmer 226 Five-Spot Card (PerkinElmer Health Sciences, Greenville, United States) to form dry blood spots (DBSs) for LC-MS/MS analysis. The sample must be taken before transfusion therapy or extracorporeal membrane oxygenation. If the sample was not taken before the administration of transfusion agents, blood should be taken no earlier than 48–72 h after the transfusion.

Whole blood samples from older children at high-risk and healthy children are collected after 4-hour fasting using a standard venipuncture method. The DBS card is prepared by applying five drops of whole blood (each ∼75 μL) to the Guthrie cards, Ahlstrom 226 filter paper, PerkinElmer 226 Five-Spot Card (PerkinElmer Health Sciences, Greenville, United States).

Samples must be dried for 4 h at room temperature and then stored at 4°C in individually labeled zippered plastic bags with desiccants or other sealed containers until analyzed by LC-MS/MS by standards of the Institute of Clinical and Laboratory Standards (CLSI, 2013). Samples must be sent to the laboratory within 5 days. In case of long-term storage of samples, it will be carried out at a temperature of −20°C. Cut-off values will be set according to the manual for the Neobase2 TM Non-derivatized MSMS kit (PerkinElmer, Wallac Oy, Turku, Finland). They will be adjusted over time as the number of samples increases.

If metabolite concentrations in dry blood spot samples exceed the cut-off values, the LC-MS/MS test will be repeated using the same dried blood spot sample the next day. If the test results show persistent abnormal results, the child will be further examined. Blood and urine are used to confirm the diagnosis. Diagnosis is confirmed by urine organic acid analysis, plasma amino acid analysis, or direct enzyme analysis. Duplicate samples are stored frozen at −20°C with a desiccating agent.

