#### 2.3.4 Diagnosis of targeted diseases (conditions)

The diseases to be analyzed in this study include AAD, OA, and FAOD, which are detected by measuring acylcarnitines, succinylacetone, and amino acids with MS/MS. For their diagnosis, the ratios of Phe/Tyr, C3/Met, C3/C2, C3/C0, С14:1/С2, С14:1/С16, С14:1/С12:1, С0/(С16+С18), and (C14 + C14:1 + C16:1)/C0 will be set. IEMs subject to diagnosis are displayed in Table 3. Limit values will be determined by studying levels of amino acids, acylcarnitines, and succinylacetone in DBSs of 750 healthy children in western Kazakhstan. In the case of normally distributed data, the cut-offs will be set to four standard deviations (SD) above or below the mean. If the distribution of analytes is skewed, reference intervals in the healthy control group will be determined nonparametrically and correspond to the 2.5–97.5th percentile of the experimental distribution. All cut-offs are subject to adjustment in light of further analyzes and additional clinical data.

**TABLE 3 T3:** Primary and repeated LC-MS/MS screening and confirmatory IEM tests.

Disorder	Primary and repeated LC-MS/MS screening	Confirmatory tests
AMINO ACIDS & UREA CYCLE DISORDERS		
PKU	↑Phe, ↑Phe/Tyr ratio	↑Phe, Phe/Tyr ratio (Blood)
		↑Phenyl acetic acid (Urine)
		Genetic sequencing of the PAH gene
MSUD	↑Val, Ile, Leu	↑Val, Ile, Leu (Blood)
	↑ Leu/Ile	↑Val, Leu/Ile, Leu/Phe ratio (Blood)
	↑Leu/Phe	↑α-KG, 2OH-IVA (Urine)
	↑Xle/Ala	Genetic sequencing of the BCKDHA, BCKDHB genes
	↑Xle/Phe	
	↑Val/Phe ratio	
HCU	↑Met, Hcy	↑Met, Hcy (Blood)
	↑Met/phe ratio	
CIT I	↑Cit	↑Cit (Blood)
		↑OA (Urine)
		Genetic sequencing of the ASS1 gene
ASA	↑Argininosuccinic acid	↑Argininosuccinic acid (Blood)
		↑Argininosuccinic acid (Urine)
		Genetic sequencing of the ASL gene
OTCD	↓Cit ↑Orn	↓Cit (Blood)
		↑ Glu (Blood)
		↑Orotic acid (Urine)
		Genetic sequencing of the OTC gene
CPS	↓Cit	↑Organic acids (Urine)
		Genetic sequencing of the CPSI gene
NAGSD	↓Cit	↓Cit (Blood)
		Genetic sequencing of the NAGS gene
TYR I	↑Tyr ↑Tyr/Phe ratio	↑ Cit (Blood)
		↑ SuAc (Urine)
		↑ OA (Urine)
		Genetic sequencing of the FAH gene
TYR II	↑Tyr	Normal levels succinylacetone (Urine)
		Genetic sequencing of the TAT gene
NKHG	↑Gly	↑Gly (Blood)
		↑Gly (CSF/P)
ARG	High arginine ↑Arg/Orn	High plasma arginine and high urinary orotic acid
ORGANIC ACID DISORDERS		
SBCAD	↑С5	Genetic sequencing of the ACADSB gene
MMA	↑C3	↑C3, C3/C2 ratio (Blood)
	↑C3/C2 ratio	↑MMA, 3OH-PA, MCA, PG (Urine)
	↑C4DC, C3/C0	

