#### 2.3.5 Confirmatory tests

Patients will be immediately referred for confirmatory tests if the results exceed the thresholds. A reanalysis of the same sample will be performed if the results fall outside the threshold. Patients will be referred for confirmatory tests if the second test also falls outside the threshold.

Confirmatory tests include:

Clinical data; analysis of therapeutic effects; reanalysis LC-MS/MS; urine analysis for organic acids by gas chromatography-mass spectrometry (GC-MS); amino acid analysis; routine blood test; blood biochemistry; blood gas analysis; tests for glucose and ammonia in the blood; tests for homocysteine, lactate and pyruvate in the blood; tests for acetone in the urine; biotin, biotin enzyme profile; measurement of enzyme activity; tests for gene mutations; DNA analysis; magnetic resonance imaging of the brain and electroencephalography.

As known, gas chromatography-mass spectrometry is one of the best methods for diagnosing congenital acidemia. As organic acids are practically not reabsorbed in the renal tubules, their concentration in urine is higher than in the blood, and they are easier to determine in urine. Patients with a positive dry blood spot test result using TMS with or without clinical manifestations of IEM will have urine organic acids determined by gas chromatography-mass spectrometry.

To determine organic acids in urine using GC-MS, collecting 10–15 mL of morning urine in a clean, dry container without preservatives and transporting it in a thermos with food ice is necessary. The urine can be frozen and stored at a temperature of −20 C0 until analysis (Gallagher et al., 2018).

Before collecting urine, appropriate instructions regarding fluid intake, consumption of certain foods, avoidance of certain medications, etc., should be followed.

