## 3 Presenting the anticipated results

### 3.1 Study outcomes

The definition applied in the present study is as follows: Inborn errors of metabolism are inherited disorders caused by mutations in genes coding for proteins that function in metabolism. In particular: Amino Acids and Urea Cycle Disorders, Organic Acid Disorders, and Fatty Acid Oxidation Disorders.

Accordingly, we apply the following definitions of measured outcomes.

• Primary outcomes:1. Normal and abnormal values of amino acids, acylcarnitines, and succinylacetone in dry blood spots of newborns and children of different age groups measured in µmol/L through liquid chromatography-tandem mass spectrometry (LC-MS/MS).

Metabolites to be measured:

Amino acids: Alanine (Ala), Arginine (Arg), Citrulline (Cit), Glutamine (Gln), Glutamic acid (Glu), Glycine (Gly), Leucine (Leu), Isoleucine (Ile), Hydroxyproline (Pro-OH), Methionine (Met), Ornithine (Orn), Phenylalanine (Phe), Proline (Pro), Tyrosine (Tyr), Valine (Val). Acylcarnitines: Free carnitine (C0), Acetylcarnitine (C2), Propionylcarnitine (C3), Malonylcarnitine+3-Hydroxybutyrylcarnitine (C3DC/C4OH), Butyrylcarnitine (C4), 2H9-C5-Methylmalonylcarnitine+3-Hydroxyisovalerylcarnitine (C4DC/C5OH), Isovalerylcarnitine (C5), Tiglylcarnitine (C5:1), Glutarylcarnitine (C5DC), Hexanoylcarnitine (C6), Octanoylcarnitine (C8), Octenoylcarnitine (C8:1), Decanoylcarnitine (C10), Decenoylcarnitine (C10:1), Decadienoylcarnitine (C10:2), Dodecanoylcarnitine (C12), Hydroxydodecenoylcarnitine (C12:1), Myristoylcarnitine (C14), Tetradecenoylcarnitine (C14:1), Tetradecadienyl-carnitine (C14:2), Hydroxytetradecanoylcarnitine (C14OH), Palmitoylcarnitine (C16), Hexadecenoylcarnitine (C16:1), 2H3-C16-3-Hydroxy-Hexadecanoylcarnitine (C16OH), 2H3-C16-3-Hydroxypalmitoleylcarnitine (C16:1OH), 2H3-Stearoylcarnitin (C18), 2H3-C18-Octadecenoylcarnitine (C18:1), 2H3-C18-Linoleylcarnitine (C18:2), 2H3-C18-3-Hydroxystearoylcarnitine (C18OH), 2H3-C18-3-Hydroxyoleoylcarnitine (C18:1OH), 2H3-C18-3-Hydroxylinoleoylcarnitine (C18:2OH). Succinylacetone (SUAC) (13C5-MPP IS).2. The number and proportion of children with detected abnormal metabolite values and checked by retesting and/or confirmatory tests if the results exceeded the thresholds.

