#### 3.2.1 Descriptive statistics and group comparison

Descriptive statistics and reference intervals for whole blood concentrations of 15 AAs, 35 ACs, and SuAc in healthy children divided into subgroups according to gender will be presented in tables. For each analyte in the healthy control group, the upper cut-off will be set above the 97.5^th^ percentile, while the lower cut-off will be set below the 2.5th percentile. Differences in the distribution of amino acids, acylcarnitines, and succinylacetone between groups, as determined using the Mann-Whitney and Kruskal-Wallis tests, will be noted in the table if found.

Cut-off values for analytes and their ratios for selective screening of AAD, OA, and FAOD presented in Table 3 will be pointed out. The results of determining the analytes in DBS in children of the healthy control group will be compared with those of previously published studies in other populations. According to the inclusion criteria, healthy newborns in the reference group must be full-term (born at 37–42 weeks). However, it should be taken into account that some of the newborns at risk for IEM are born prematurely. In this regard, it is also necessary to determine reference intervals for the concentrations of 15 AAs, 35 ACs and SuAc in dried blood spots of premature infants who do not have clinical symptoms of IEM.

Comparison of mean concentrations (Me, range) of analytes between groups of high-risk children and healthy controls will be presented.

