### 3.5 Presenting positive and false positive cases

Even though the number of false positive results during LC-MS/MS is much lower than when using standard biochemical tests and, according to different researchers, ranges from 1.9% to 2.3% (Selim et al., 2014; Hassan et al., 2016), we assume that a certain number of samples will turn out to be a false positive. The number of true and false positives for each disease according to each disorder after the primary (baseline) LC-MS/MS will be established. Positive predictive values will be calculated by the total number of true positive cases divided by the total number of true positive and false positive cases.

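### Primary outcome 2 and the retest triggers are counted per child but rest on per-analyte cut-offs, with no rule for combining about 51 analytes and no link to Table 3

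*Protocol article*

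**What the plan says.** **Outcome.** Section 3.1 of the protocol article defines primary outcome 2 as "The number and proportion of children with detected abnormal metabolite values", and goes on to include their retest or confirmatory check where a threshold was passed. The unit is the child. No number of analytes, pattern or direction is given, and Table 3 is not mentioned.

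**Triggers.** Section 2.3.1: "If metabolite concentrations in dry blood spot samples exceed the cut-off values, the LC-MS/MS test will be repeated", using the same spot the next day. Section 2.3.5: "A reanalysis of the same sample will be performed if the results fall outside the threshold". Section 2.3.5 also sends children above the thresholds straight to confirmatory tests, which does not fit easily with reanalysing first.

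**Cut-offs, all per analyte.**
- Section 2.3.1: the kit manual's values (not given), to be adjusted over time.
- Section 2.3.4: for normally distributed analytes, "the cut-offs will be set to four standard deviations (SD) above or below the mean"; for skewed ones, the 2.5th and 97.5th percentiles.
- Section 3.2: for skewed analytes, the 0.5th and 99.5th percentiles.
- Section 3.2.1: for every analyte, an upper cut-off above the 97.5th percentile, while "the lower cut-off will be set below the 2.5th percentile".

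**Table 3.** Section 2.3.5 describes it as giving the criteria for primary and repeated screening. It lists directional markers and ratios by disorder, but does not say whether one listed marker is enough or whether marker and ratio must both be abnormal.

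**Benchmark.** Section 3.5 cites other studies for a false-positive rate that "ranges from 1.9% to 2.3" per cent.

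**The concern.** A limit that 5% of healthy children fall outside is reasonable as a reference interval for one analyte. Applied to about 51 analytes at once, with one value enough to count the child, it flags a large share of children who have no inborn error. This includes values in directions that no Table 3 disorder uses, such as low phenylalanine.

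The plan does not say whether it intends this. The outcome and the triggers are worded openly, section 3.2.1 sets two limits for each analyte, and nothing connects these to a decision about a child.

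At stake are the meaning of a primary outcome, the predictive values planned in sections 3.2 and 3.5, and the confirmatory workload, since section 2.3.5 plans urine organic acid analysis for every child with a positive blood spot.

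**Working it through.** **Inputs from the plan**
- Analytes: "reference values for 15 AAs, 35 ACs, and SuAc" (section 2.1), so k = 15 + 35 + 1 = 51. Section 2.3.2 implies 52 by counting free carnitine separately; the list in section 3.1 contains 47.
- Share of unaffected children outside the limits, per analyte: a = 5% (2.5–97.5), 1% (0.5–99.5) or 0.0063% (4 SD, both tails, normal distribution).
- Section 3.2 expects free carnitine and acylcarnitines to be non-normal, so the 4 SD rule would not normally cover them.
- Frequency of inborn errors: 2%–2.5% (section 2.2.1). At 2%, 30 of the 1,500 are affected and 1,470 are not.

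**Assumptions of this review.** Unaffected referred children follow the healthy reference distribution. Correlations are illustrative (equicorrelated normal values, 100,000 simulated children).

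**The cited figure.** The 1.9–2.3% cannot be reproduced, because the article gives neither its denominator nor its decision rule. Over 51 independent analytes it would need 1 − (1 − 0.019)^(1/51) = 0.038% to 1 − (1 − 0.023)^(1/51) = 0.046% outside per analyte. None of the plan's numeric cut-offs gives that.

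**Chance that an unaffected child has at least one value outside:** 1 − (1 − a)^k

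| Cut-off rule | Independent | r = 0.3 | r = 0.5 |
|---|---|---|---|
| 2.5–97.5, all 51 (section 3.2.1) | 1 − 0.95^51 = 92.7% | 81% | 63% |
| 4 SD for 15 amino acids, 2.5–97.5 for the other 36 (section 2.3.4) | 1 − 0.999937^15 × 0.95^36 = 84.2% | 71% | 55% |
| 0.5–99.5, all 51 (section 3.2) | 1 − 0.99^51 = 40.1% | 30% | 21% |
| 4 SD, all 51 | 1 − 0.999937^51 = 0.3% | 0.3% | 0.3% |

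At r = 0.7 the first row falls to 41% and the third to 13%. With k = 47 or 52 the first entry is 91.0% or 93.1%. If only upward exceedances counted, it would be 1 − 0.975^51 = 72.5%.

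**Narrowest Table 3 reading.** Eight signals stand as the only measured marker for at least one disorder: raised Cit, lowered Cit, raised Tyr, Gly, C4, C5, C5-OH and C10:2. Counting these alone:
- 2.5% per tail: 1 − 0.975^8 = 18.3%
- 0.5% per tail: 1 − 0.995^8 = 3.9%

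**What this means in 1,500 children.** Even if all 30 affected children were flagged, the pooled positive predictive value after the first run would be at most:
- 2.5–97.5, all analytes: 1,470 × 0.927 = 1,363 false positives; 30/1,393 = 2.2%
- 0.5–99.5, all analytes: 1,470 × 0.401 = 589; 30/619 = 4.8%
- eight tails at 2.5%: 1,470 × 0.183 = 269; 30/299 = 10%
- 4 SD, all analytes: 1,470 × 0.0032 = 5; 30/35 = 86%

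**Retest.** Rerunning the same spot removes only analytical noise. With independent analytes, 2.5–97.5 limits and an assumed analytical share of variance of 5% to 30%, 84% down to 58% of unaffected children still have an analyte abnormal on both runs.

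**The case against.** The strongest reply is that nowhere does the plan write that any one of 51 values suffices. Its framing is by disorder: section 2.3.5 points to Table 3, section 3.2.1 links cut-offs and ratios to Table 3, and section 3.5 counts true and false positives by disease. This stands, so the any-one rule is the literal reading of open wording and not a stated rule. It does not remove the problem: outcome 2 and the triggers do not refer to Table 3, Table 3 does not say how its markers combine, and its single-marker signals alone give 4–18%.

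A reader might infer that most unaffected children will be flagged whichever cut-off is used. The documents do not support that. It needs the 2.5–97.5 limits and no more than moderate correlation. It fails at 0.5–99.5 (40% or less) and at 4 SD throughout (0.3%). Section 3.2.1 also places its cut-offs beyond the percentiles, so 5% per analyte is an upper bound, and the kit-manual values are unknown. The size of the problem therefore depends heavily on the cut-off conflict. Settling that conflict on either percentile pair would still leave 93% or 40% under independence.

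A reader might also infer that the plan contradicts its own expected false-positive rate. It does not. The 1.9–2.3% is what other researchers report; for this study section 3.5 expects only some false positives.

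Finally, outcome 2 also covers retest and confirmation, and section 3.2 separately defines a detection rate based on diagnosed cases. That rate remains interpretable.

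A condensed article may leave laboratory detail elsewhere, but the outcome and the conflicting cut-offs are what this article chose to state.

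**Conclusion.** The point holds as a missing decision rule, made serious by conflicting cut-offs. For the same primary outcome, the plan's text allows a flag rate among unaffected children anywhere from 0.3% to about 93%. The low end needs 4 SD limits for every analyte, which the plan's own statement about carnitines makes unlikely. Under the percentile limits, outcome 2 and the first-run predictive values would largely reflect how many analytes are measured.

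The figures rest on the any-one reading, on unaffected referred children resembling the healthy reference group (sick children would probably exceed it), and on assumed correlations. The cited 1.9–2.3% serves only as a literature benchmark; its definition cannot be checked from the article.

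**What to change.** 1. Define outcome 2 per child as meeting a Table 3 disorder criterion in its listed direction, and use the same definition in sections 2.3.1 and 2.3.5.
2. Have the investigators state in advance how markers and ratios combine within each disorder. This review does not prescribe the referral rule.
3. Reconcile the cut-off and trigger statements in sections 2.3.1, 2.3.4, 2.3.5, 3.2 and 3.2.1.
4. Keep the 2.5–97.5 intervals as descriptive reference intervals, separate from the screening cut-offs.
5. Before analysing the 1,500, apply the full algorithm to the 750 healthy children and report the child-level flag rate with its confidence interval. The 95% half-width is at most 1.96 × √(0.25/750) = 3.6 percentage points. Note that the rate is optimistic if the same children set the limits.
6. Report the count of children with any analyte outside its interval alongside, labelled as such.

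The cost is wording plus one extra analysis of data already planned for collection. The small downside is a lower headline count of abnormal children.

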### 3.3 Presenting detected cases

The results of LC-MS/MS in affected individuals will be presented as metabolic profiles. The metabolic profile of each affected individual will be placed next to the metabolic profile of a healthy individual from the control group, corresponding to gender, age, and place of residence. IEMs detected, their frequency, primary clinical manifestations, and main diagnostic markers in high-risk children confirmed by LC-MS/MS will be described in the tables. The average age of patients at the time of diagnosis will also be recorded. Table 4 displays the most common clinical manifestations in patients diagnosed with IEM. This list can be expanded by the results obtained in the study.

**TABLE 4 T4:** Common features encountered in children with different IEM (N = ***).

Variables	Number of patients (percent)
Developmental delay	
Neurological abnormalities	
Disturbed consciousness level	
Vomiting/dehydration	
Hyperammonemia	
Metabolic acidosis	
MRI brain abnormalities	
Infections	
Hypoglycemia	
Mental retardation	
Organomegaly	
Micro/macrocephaly	
Ophthalmic abnormalities	
Cardiomyopathy	
Seizures	
Tachypnea	
Thrombocytopenia	
Abnormal smell	
Hair growth disorders	
Osteoarticular anomalies	
Abnormal muscle tone	
Mutism	
Dysmorphia	

The baseline and repeated LC-MS/MS analysis results and biochemical confirmation in children diagnosed with IEM, according to the diagnosed disease, will also be presented. Demographic and laboratory data of confirmed cases detected by LC-MS/MS among 1,500 Kazakhstani children with suspected IEM will be presented in Table 5. Also, the table will include data on the reference values of the considered metabolites obtained in a sample of healthy controls.

**TABLE 5 T5:** Cases detected by LC-MS/MS among 1,500 children suspected IEM.

Metabolic disorder	Metabolite detected by LC- MS/MS (Abnormal parameter)	Positive cases, n (%)	Concentration mean (range) (μmol/L)	Cut-off limit (μmol/L)	References range (μmol/L)	Province (oblast), positive cases (n)
						
						

IEM, identified by selective screening with calculated frequencies for each disease, will be described separately for diseases belonging to the AAD, OA, and FAOD groups.

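### Primary outcome 2 counts screen positives checked only by a rerun of the same spot, and the protocol's conflicting accounts of confirmation leave the case definition behind detection rate, PPV and incidence open

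*Protocol article*

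**What the plan says.** Section 3.1 lists two primary outcomes: the metabolite values themselves, and "The number and proportion of children with detected abnormal metabolite values and checked by retesting and/or confirmatory tests if the results exceeded the thresholds". Urine organic acids and gene tests appear in the same section as surrogate endpoints. The tasks at the end of the Introduction are to assess the burden of these disorders and to analyse the prevalence of each.

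On the retest, section 2.3.1 says that "the LC-MS/MS test will be repeated using the same dried blood spot sample the next day", and then: "If the test results show persistent abnormal results, the child will be further examined".

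Confirmation is described in five places:

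- **Abstract:** clinical signs, blood metabolites, urine organic acids and gene tests, joined by *and*.
- **Section 2.3.1:** "Diagnosis is confirmed by urine organic acid analysis, plasma amino acid analysis, or direct enzyme analysis". Sequencing is not mentioned.
- **Section 2.3.5:** a long list that opens with "Clinical data; analysis of therapeutic effects; reanalysis LC-MS/MS" and also includes urine organic acids, enzyme activity and gene tests. It does not say which or how many suffice.
- **Table 3:** primary and repeated LC-MS/MS share the screening column. Confirmatory tests have their own column, specific to each disorder and often including sequencing.
- **Section 3.3:** tables will show "main diagnostic markers in high-risk children confirmed by LC-MS/MS".

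On routing, section 2.3.5 begins with "Patients will be immediately referred for confirmatory tests if the results exceed the thresholds", and its next two sentences put a reanalysis of the same sample before referral.

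Section 3.2 divides diagnosed cases by screened children for the detection rate, and true positives by true plus false positives for PPV. Section 3.4 relates IEM cases to regional births. Section 3.5 counts true and false positives after the first LC-MS/MS run.

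**The concern.** The study is meant to say how common these disorders are, yet the primary outcome that counts children does not count disease. A rerun of the same spot repeats the index test on the same specimen. It can catch an analytical error, but it is not independent evidence of a disorder. The wording does not even require the rerun to be abnormal.

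The looseness reaches the derived results by a second route. Detection rate, PPV and incidence all need a rule for who is a case, and the protocol offers several that disagree. The sharpest conflict is that repeat LC-MS/MS is screening in Table 3 and a confirmatory test in section 2.3.5. Under the second reading the index test can enter its own reference standard. The choice could then be made after the data are seen, and comparison with other populations, which is task 3, would depend on it.

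**Working it through.** **Step 1. The confirmation rules side by side**

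| Place | Repeat LC-MS/MS confirms? | Sequencing included? | Rule |
|---|---|---|---|
| Abstract | not listed as such | yes | elements joined by *and* |
| 2.3.1 | no | no | any one of three biochemical tests |
| 2.3.5 | yes | yes | list, no decision rule |
| Table 3 | no, it is screening | yes, many rows | by disorder; any or all lines not stated |
| 3.3 | wording suggests yes | not mentioned | description of a table |

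Table 3 has 37 rows (12 amino acid and urea cycle, 14 organic acid, 11 fatty acid oxidation). In 8 of them sequencing is the only confirmatory test listed: SBCAD, MHBDD, 3HMG, VLCAD, LCHAD, CPT II, CACT and DE RED. The MCAT confirmatory cell is blank in the text available, which may be a loss in reading the PDF.

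**Step 2. Inputs for the size**

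- N = 1,500 screened children and p = 2% to 2.5% IEM frequency (section 2.2.1).
- f = 1.9% to 2.3% false positives (section 3.5). This is cited from other studies and its denominator is not given.
- s = share of first-run false positives that stay abnormal on the rerun and are called cases. The protocol gives no value, so a range is shown.
- Assumed: every true case is positive on the first run.

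The protocol states no expected number of cases, so there is no figure of its own to reproduce.

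**Step 3. Formulas**

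- True cases T = N × p. False positives F = N × f.
- Case count under a loose rule = T + sF. Ratio to the strict count = 1 + sF/T.
- First-run PPV = (T + sF)/(T + F). The denominator does not change with s.

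**Step 4. Results**

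| p | f | T | F | T + F | Ratio, s = 1 | Ratio, s = 0.5 | Ratio, s = 0.25 | PPV, s = 0 | PPV, s = 0.5 |
|---|---|---|---|---|---|---|---|---|---|
| 2.0% | 1.9% | 30 | 28.5 | 58.5 | 1.95 | 1.48 | 1.24 | 0.51 | 0.76 |
| 2.0% | 2.3% | 30 | 34.5 | 64.5 | 2.15 | 1.58 | 1.29 | 0.47 | 0.73 |
| 2.5% | 1.9% | 37.5 | 28.5 | 66 | 1.76 | 1.38 | 1.19 | 0.57 | 0.78 |
| 2.5% | 2.3% | 37.5 | 34.5 | 72 | 1.92 | 1.46 | 1.23 | 0.52 | 0.76 |

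If f applies to unaffected children only, F = (1,500 − T) × f and the s = 1 ratios run from 1 + 27.8/37.5 = 1.74 to 1 + 33.8/30 = 2.13.

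Detection rate and incidence have fixed denominators, so the same ratios apply to them. At s = 1 the proportion of screened children is 58.5/1,500 = 3.9% to 72/1,500 = 4.8%, against 2.0% to 2.5% for true cases, and PPV is 1 by construction.

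**The case against.** The strongest reply is that outcome 2 is a screening yield, which always exceeds the number of confirmed cases, and that it is not the numerator of anything else. This is right as far as it goes. A reader might infer that outcome 2 feeds detection rate, PPV and incidence directly. It does not: sections 3.2 and 3.4 use diagnosed cases, true positives and IEM cases. What stands is that those terms are tied to no single confirmation rule.

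A reader might also infer that disorders with only sequencing in Table 3 can never be confirmed under section 2.3.1. That does not follow. Section 2.3.1 allows enzyme analysis for any disorder, and section 2.3.5 provides urine organic acids for every child with a positive spot. The supportable point is narrower: section 2.3.1 omits a test that Table 3 relies on.

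Nor do the documents support saying that the case count will double or that PPV will be 100%. The cited false-positive rate comes from outside studies, says nothing about persistence, and section 3.5 applies the concept to the first run. Section 2.3.1 sends persistent abnormal results for further examination, section 3.5 expects false positives, and section 3.3 plans to show repeat results and biochemical confirmation in diagnosed children. The section 3.3 phrase about confirmation by LC-MS/MS may be loose drafting. These points limit the size of the problem. They do not supply the missing rule.

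**Conclusion.** The concern holds in this form: a primary outcome that admits unconfirmed screen positives, no primary outcome for confirmed IEM, and stated confirmation rules that conflict. This is contradiction in the text rather than detail left to an analysis plan.

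The effect on the case count is at most about 1.7- to 2.1-fold (1.74 to 2.15 across the two denominators). That bound requires every first-run false positive to persist and be called a case. It falls to about 1.4- to 1.6-fold if half do and about 1.2- to 1.3-fold if a quarter do. All of these rest on the protocol's assumed 2–2.5% frequency, the cited 1.9–2.3% rate taken per child, and full first-run detection of true cases. The actual persistence is unknown.

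The plan should be changed, and the change needs no new tests.

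**What to change.** 1. Reword primary outcome 2 as the number and proportion of screened children with confirmed IEM.
2. Adopt one case definition for analysis, by disorder, based on the Table 3 confirmatory column. State for each row whether any or all of the listed lines are needed. Do not accept LC-MS/MS reanalysis of the screening spot as sole proof. Where a row lists blood markers already measured at screening, say which specimen and test count.
3. Use confirmed cases as the numerator for detection rate and incidence and as the true positives for PPV. Align the Abstract and sections 2.3.1, 2.3.5 and 3.3 with that definition.
4. Report first-positive, repeat-positive and confirmed counts as separate stages, so that the screening yield is still visible.
5. Check the MCAT confirmatory cell.
6. Reconcile the referral wording within section 2.3.5 and between it and section 2.3.1. Which sequence is right is for the investigators to settle.

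The cost is a smaller headline proportion and some work on Table 3, more than one cell, because the multi-line rows need a decision rule. The tests are already planned.
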